# Intermittent Versus Continuous Low-Energy Diet in Patients With Type 2 Diabetes: Protocol for a Pilot Randomized Controlled Trial

**DOI:** 10.2196/21116

**Published:** 2021-03-19

**Keywords:** type 2 diabetes, diabetes, diabetic diet, low-energy diet, low calorie diet, intermittent energy restriction, intermittent fasting, diabetes remission, smartphone, mobile phone, mHealth, mobile health

## Abstract

**Background:**

Intensive face-to-face weight loss programs using continuous low-energy diets (CLEDs) providing approximately 800 kcal per day (3347 kJ per day) can produce significant weight loss and remission from type 2 diabetes (T2D). Intermittent low-energy diets (ILEDs) and remotely delivered programs could be viable alternatives that may support patient choice and adherence.

**Objective:**

This paper describes the protocol of a pilot randomized controlled trial to test the feasibility and potential efficacy of remotely supported isocaloric ILED and CLED programs among patients with overweight and obesity and T2D.

**Methods:**

A total of 79 participants were recruited from primary care, two National Health Service hospital trusts, and a voluntary T2D research register in the United Kingdom. The participants were randomized to a remotely delivered ILED (n=39) or CLED (n=40). The active weight loss phase of CLED involved 8 weeks of Optifast 820 kcal/3430 kJ formula diet, followed by 4 weeks of food reintroduction. The active weight loss phase of ILED (n=39) comprised 2 days of Optifast 820 kcal/3430 kJ diet and 5 days of a portion-controlled Mediterranean diet for 28 weeks. Both groups were asked to complete 56 Optifast 820 kcal/3430 kJ days during their active weight loss phase with an equivalent energy deficit. The diets were isocaloric for the remainder of the 12 months. CLED participants were asked to follow a portion-controlled Mediterranean diet 7 days per week. ILED followed 1-2 days per week of a food-based 820 kcal/3430 kJ diet and a portion-controlled Mediterranean diet for 5-6 days per week. Participants received high-frequency (weekly, fortnightly, or monthly depending on the stage of the trial) multidisciplinary remote support from a dietitian, nurse, exercise specialist, and psychologist via telephone or the Oviva smartphone app. The primary outcomes of the study were uptake, weight loss, and changes in glycated hemoglobin at 12 months. An outcome assessment of trial retention was retrospectively added. Secondary outcomes included an assessment of adherence and adverse events. A qualitative evaluation was undertaken via interviews with participants and health care professionals who delivered the intervention.

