### Interventions

Figure 1 shows a summary of the 2 dietary programs. Both included a combination of the Optifast LED and the Mediterranean diet over a period of 12 months. Both programs were designed to have exactly 56 Optifast LED days and an equivalent level of energy restriction during their active weight loss phase and weight maintenance or continued weight loss phase.

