#### CLED

##### Active Weight Loss Phase (12 weeks)

Weeks 1 to 8 involved the Optifast LED (Néstle Health Science, United Kingdom). This provided approximately 820 kcal (3430 kJ) per day and consisted of 3 sachets per day of Optifast (200 kcal/837 kJ per sachet of shake or soup made with water) in addition to 8×80 g portions of nonstarchy vegetables (approximately 140 kcal/586 kJ), one dessertspoon of oil per day (80 kcal per 335 kJ), and 2-2.5 liters of calorie-free fluids. The participants were asked to avoid alcohol and excessive caffeine to minimize the risk of dehydration. Participants who were unable to tolerate Optifast were offered a food-based LED with a similar macronutrient profile. This comprised 250 g of lean protein foods (eg, lean meat, fish, eggs, and vegetarian proteins), 5 portions of nonstarchy vegetables, 3 portions of low-fat dairy (eg, 200 ml milk), one portion of unsaturated fat (eg, small handful nuts), one portion of fruit, and one carbohydrate portion (eg, slice of bread). Participants reported their adherence to the LED days throughout the trial during their regular contact with the dietitian.

Diet reintroduction in weeks 9-12 allowed a food-based, energy-restricted Mediterranean diet providing 1000 kcal (4184 kJ) daily in week 1, 1200 kcal (5021 kJ) daily in week 2, 1400 kcal (5858 kJ) daily in week 3, and 1500 kcal (6276 kJ) daily in week 4.

The Mediterranean diet, as described previously by Harvie et al [43], was relatively high in protein (25% energy) with moderate carbohydrate (45% energy from low glycemic load carbohydrates), moderate fat (30% energy from fat: 15% monounsaturated, 8% polyunsaturated, and 7% saturated fatty acids), and limited alcohol to <10 units per week.

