##### Weight Maintenance or Continued Weight Loss Phase (40 Weeks)

Participants who achieved a trial weight loss goal of 15%, and/or their target weight if greater, were advised to follow a euenergetic Mediterranean diet for weight maintenance. Those who had not achieved 15% weight loss or wished to lose more weight were asked to follow a 25% energy-restricted Mediterranean diet. Individuals’ estimated energy requirements were calculated using the Mifflin equations [44] to estimate the basal metabolic rate×reported metabolic equivalent of the task. These calculations were based on the revised weight and activity levels after the completion of the active weight loss phase.

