##### Weight Maintenance or Continued Weight Loss Phase (24 weeks)

Participants were asked to follow a food-based ILED. Participants who had achieved 15% weight loss, and/or their target weight if greater, were asked to follow the food-based LED described above for one day per week and a euenergetic Mediterranean diet aimed at weight maintenance (eg, 2550 kcal [10,669 kJ] per day for a 50-year-old man, BMI 34) for 6 days. Participants who had not achieved 15% weight loss or wished to lose more weight were asked to follow the food-based LED for 2 consecutive days per week and an energy-restricted Mediterranean diet (eg, 2100 kcal [8786 Kj] per day for a 50-year-old man, BMI 34) for 5 days. This provided an overall daily 25% energy restriction through the week.

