## Discussion

This is the first study to compare an ILED with an isocaloric CLED to achieve and maintain weight loss and normoglycemia among patients with T2D and overweight and obesity. The study will inform the acceptability and potential efficacy of high-frequency remote follow-up in patients with T2D and overweight and obesity undertaking low energy diets. It will also contribute to the limited data on the safety and efficacy of patients with T2D on insulin undertaking a ILED or CLED. The study did not have a standard or best practice control group for comparison and was not powered to show statistical differences between the groups. However, the planned quantitative and qualitative analyses will assess the feasibility of the programs and inform the case for a future definitive trial.

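### The diets are matched on total deficit in active phases of unequal length and only on daily restriction afterwards, so the two programmes are not isocaloric over 12 months

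*Protocol article*

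**What the plan says.** The abstract (Methods) gives both arms 56 formula days with an equivalent deficit in the active phase and then adds: "The diets were isocaloric for the remainder of the 12 months". The Interventions section claims "an equivalent level of energy restriction during their active weight loss phase and weight maintenance or continued weight loss phase". The abstract's Objective and Goals of This Study describe the programmes as isocaloric, and the Discussion opens with "This is the first study to compare an ILED with an isocaloric CLED to achieve and maintain weight loss and normoglycemia".

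The phases differ in length. CLED has 12 active weeks followed by 40 weeks of maintenance or continued loss; ILED has 28 followed by 24. In the ILED active phase, a deficit of up to 265 kcal is applied on Mediterranean-diet days to make the two active phases isocaloric.

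In the later phase the CLED rule is "Those who had not achieved 15% weight loss or wished to lose more weight were asked to follow a 25% energy-restricted Mediterranean diet". The ILED rule for the same participants is two low-energy days and five restricted days a week: "This provided an overall daily 25% energy restriction through the week". Participants at goal move to approximate energy balance in both arms.

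The primary weight and HbA1c outcomes are read at 12 months.

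**The concern.** Two different quantities are equalised over two different durations. Active phases of 12 and 28 weeks can be isocaloric only in total. Later phases of 40 and 24 weeks are equalised only per day. Totals over 52 weeks then need not agree, yet the article calls the programmes isocaloric, and 52 weeks is where the primary efficacy outcomes are read.

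What is at stake is the meaning of the 12-month results. A reader told that the diets are isocaloric will take any difference at week 52 as an effect of pattern, intermittent against continuous, when the amount of restriction prescribed may also have differed. The results are meant to inform the decision on a full trial, so the description of what was compared should be right.

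**Working it through.** **Inputs, all from the article.** CLED weeks 1–8: "This provided approximately 820 kcal (3430 kJ) per day", for 56 days. CLED weeks 9–12: "providing 1000 kcal (4184 kJ) daily in week 1, 1200 kcal (5021 kJ) daily in week 2, 1400 kcal (5858 kJ) daily in week 3", then 1500 kcal in week 4. ILED active phase: 56 days at 820 kcal and 140 Mediterranean days with deficit d. Later phase below goal: 25% restriction for 280 days (CLED) or 168 days (ILED). Let E be the daily requirement at the start and E′ the requirement after the active phase; the CLED section says requirements were recalculated then.

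**Step 1: reproduce the 265 kcal figure.**
- CLED active deficit = 56(E − 820) + 7[(E − 1000) + (E − 1200) + (E − 1400) + (E − 1500)] = 84E − 81,620.
- ILED active deficit = 56(E − 820) + 140d.
- Setting the totals equal gives d = (28E − 35,700)/140 = 0.2E − 255.
- At E = 2600, d = 520 − 255 = 265, exactly the stated ceiling.

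So the active phases are matched on total deficit. They are not matched per day: at E = 2600 the total is 136,780 kcal in each arm, which averages 136,780/84 = 1628 kcal/day on CLED and 136,780/196 = 698 kcal/day on ILED.

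**Step 2: the requirement implied by the ILED example.** (5 × 2100 + 2 × 820)/7 = 1734 kcal/day. At 25% restriction the requirement is 1734.3/0.75 = 2312 kcal/day. The at-goal example agrees closely: (6 × 2550 + 820)/7 = 2303 kcal/day.

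**Step 3: later phase, 25% restriction throughout.** CLED: 280 × 0.25E′ = 70E′. ILED: 168 × 0.25E′ = 42E′. Difference: 28E′, which is 64,736 kcal at E′ = 2312.

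**Step 4: prescribed totals over 52 weeks.**

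| E | E′ | CLED (kcal) | ILED (kcal) | Gap (kcal) | Ratio |
|---|---|---|---|---|---|
| 2312 | 2312 | 274,428 | 209,692 | 64,736 | 1.31 |
| 2600 | 2312 | 298,620 | 233,884 | 64,736 | 1.28 |
| 1800 | 1800 | 195,580 | 145,180 | 50,400 | 1.35 |
| 2600 | 2100 | 283,780 | 224,980 | 58,800 | 1.26 |
| 3000 | 3000 | 380,380 | 285,180 | 95,200 | 1.33 |

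The last three rows use assumed requirements. In the last, the 265 kcal ceiling binds (d would need to be 345), so the active phases no longer match either: 140 × 80 = 11,200 kcal of that gap comes from the ceiling.

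**Step 5: where the gap sits.** Weeks 13–28 are 112 days, and 112 × 0.25E′ = 28E′. In those weeks CLED is already on 25% restriction, while ILED is still working through the deficit that CLED completed by week 12. At E = 2600 and E′ = 2312 the week-28 totals are 201,516 (CLED) and 136,780 (ILED). Weeks 29–52 then add 97,104 to each.

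**Step 6: other goal combinations at the end of the active phase (E′ = 2312).** Both at goal: about zero. CLED at goal and ILED not: ILED is ahead by 42E′ = 97,104 kcal.

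**The case against.** The sentences about the later phase have a true reading. The Interventions section speaks of a level of restriction, phase by phase, and both arms do follow the same 25% rule once both are in the later phase. That stands, but both arms are in that phase only in weeks 29–52, and equal daily rates over 280 and 168 days do not make the programmes isocaloric. The phase lengths are stated openly, and the article acknowledges faster early loss on CLED, so nothing is hidden. Faster loss, however, is not the same statement as a larger prescribed total.

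The 15% goal can also close the gap. If a participant moves to energy balance whenever goal is reached, two fully adherent participants who both reach it within the year end with about the same total. This stands, and it confines the figures above to participants prescribed 25% throughout.

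Reading the 2550 kcal example as the requirement itself gives ILED a 1 − 1734/2550 = 32% restriction and cuts the CLED excess to about 15% (311,080 against 269,620 kcal at E = E′ = 2550). That contradicts the stated 25%, and CLED is still higher.

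Finally, this is a pilot. It plans no significance tests on the primary outcomes, gives confidence intervals for change within each group, and says it is not powered for group differences. No planned inference depends on equal totals, which limits the severity.

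Three stronger readings are tempting and unsupported:
- **A kilogram advantage for CLED.** At an assumed 7700 kcal/kg the first-row totals would imply losses of 35.6 and 27.2 kg. The smaller of these is under 15% only for someone above about 181 kg (27.2/0.15). A participant below goal all year has therefore largely not achieved the prescribed deficit, and prescribed kcal cannot be turned into kilograms.
- **A CLED excess at arm level.** Step 6 shows that the direction depends on who reaches goal in each arm.
- **Most participants being below goal.** The benchmark trial in the Introduction reports 31 of 36 in remission among those with 15% loss. The article does not say that all 36 were in the intervention arm, nor what their status was when the initial diet phase ended.

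**Conclusion.** The point holds as a misdescription of the comparison. The programmes are matched for total prescribed deficit in the active phase, up to a requirement of 2600 kcal/day, and for daily restriction afterwards. They are not matched for total deficit over 12 months, although the abstract, Goals of This Study and Discussion imply that they are.

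For a participant prescribed 25% restriction through the whole later phase in either arm, CLED carries 28E′ kcal more: about 65,000 kcal, or 28–31% more, on the article's example figures. The requirement is inferred from that example and from the 265 kcal ceiling, not stated directly; over assumed requirements of 1800–3000 kcal/day the excess is about 26–35%. The figures are prescribed deficits; adherence and the optional relapse weeks are not modelled. The direction for a whole arm is not fixed. A difference at week 52 could therefore reflect amount as well as pattern of restriction, but the documents do not show that it must. The correction concerns the description and labelling; the planned descriptive analysis is not invalidated.

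**What to change.** Reconcile the abstract (Objective and Methods), Goals of This Study, Interventions and the Discussion. State that the diets are matched for total prescribed deficit in the active phase, within the 265 kcal ceiling, and for daily restriction afterwards, and that total prescribed deficit over 12 months is not matched. Label the week-52 weight and HbA1c results as a contrast of whole programmes, not of isocaloric diets that differ only in pattern.

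Optionally, report prescribed restriction by arm descriptively: numbers on 25% restriction and on maintenance, and weeks spent on each. Say that this depends on weight-loss status after randomisation and so cannot serve as a baseline-type adjustment.

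No change to either diet is proposed. The cost is a few sentences and, if the option is taken, one descriptive table. The downside is a weaker isocaloric headline.

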**Results:**

A total of 79 overweight or obese participants aged 18-75 years and diagnosed with T2D in the last 8 years were recruited to the Manchester Intermittent and Daily Diet Diabetes App Study (MIDDAS). Recruitment began in February 2018, and data collection was completed in February 2020. Data analysis began in June 2020, and the first results are expected to be submitted for publication in 2021.

**Conclusions:**

The outcomes of the MIDDAS study will inform the feasibility of remotely delivered ILED and CLED programs in clinical practice and the requirement for a larger-scale randomized controlled trial.

**Trial Registration:**

International Standard Randomized Controlled Trial Number (ISRCTN) 15394285; http://www.isrctn.com/ISRCTN15394285

**International Registered Report Identifier (IRRID):**

DERR1-10.2196/21116

## Introduction

### Background

An estimated 4.7 million people have type 2 diabetes (T2D) in the United Kingdom, with the number expected to rise to over 5.5 million by 2030 [1]. Diabetes related complications are common, and people with T2D die up to 10 years earlier than those without the disease [2]. Currently, 10% of the National Health Service (NHS) budget in the United Kingdom is spent on diabetes (approximately £10 billion (US $13.8 billion) per year) [1].

Approximately 80% to 90% of people with T2D have overweight or obesity [3-6]. Clinical guidelines for the management of T2D focus largely on multiple drug treatments to reduce blood glucose. They also recommend at least 5% to 10% weight loss [7,8] as this leads to improvements in glycemic control, insulin sensitivity, blood lipids, and blood pressure (BP) [9,10].

### Continuous and Intermittent Low-Energy Diets

Intensive face-to-face weight loss programs using continuous low-energy diets (CLEDs) that provide approximately 800 kcal (3347 kJ) per day of formula-based total diet replacement for 8 to 20 weeks or longer are highly effective for large weight loss and remission from T2D [11-14]. The recently published Diabetes Remission Clinical Trial (DiRECT) tested an intensive CLED program in primary care and found that it was superior to standard best practice care (standard daily moderate energy restriction advice with minimal support). At 12 months, 45.6% (68/149) participants of the intervention group achieved remission with an average weight loss of 10 kg compared with 4.0% (6/149) and 1 kg loss in the control group (*P*<.001). Remission was highest (31/36, 86%) in those who achieved 15% weight loss [13] and is more likely in those diagnosed with T2D in more recent years [15].

The CLED approach using total diet replacement is thought to be effective because the initial rapid weight loss can be highly motivating [16], and formula diets remove decision making around food choices. In addition, subjective hunger may be reduced by the associated ketosis [17]. CLEDs have been shown to reduce excess fat in the liver and pancreas in patients with T2D, which is part of the proposed mechanism for T2D remission [11,18].

Possible drawbacks of the CLED approach are that it is not appealing to or achievable for everyone. Participants following CLED programs report shame and awkwardness in social situations centered around food [19]. Attrition in intensive CLED studies on people with overweight or obesity (+/−T2D) is approximately 25% [13,20], although higher rates have been reported in studies with less frequent health care professional (HCP) contact [14]. The prevention of weight gain following a CLED program remains a key challenge. In 2 years, participants in the CLED group in the DiRECT trial appeared to have regained approximately 40% of the weight they had lost after the initial total diet replacement phase despite regular face-to-face support and an intensive 2-year relapse program involving repeated spells of a CLED, partial meal replacements, and antiobesity medications [13,21].

An intermittent low-energy diet (ILED) is a potential alternative to CLED. This includes the same number of low-energy formula diet days as CLED, but these days are undertaken for 2 days per week over a longer period. ILED may provide an alternative approach for people who find CLEDs unappealing or difficult to maintain. Qualitative reports on people following CLEDs suggest that they would prefer an intermittent approach that may be easier to fit into life without the need for weeks away from normal food [22].

A recent randomized controlled trial (RCT) in people with T2D compared an ILED with regular, daily, modest energy restriction (1200-1500 kcal/5020-6276 kJ per day) for 12 months and showed similar improvements to glycemic control in both groups [23]. Early studies of CLEDs show that some of the improvements in insulin sensitivity and beta cell function are associated with acute energy restriction rather than weight loss [24]. As these benefits subsequently attenuate when subjects enter weight maintenance with euenergetic feeding [25], ongoing spells of intermittent energy restriction each week may be a way to maintain beneficial glycemic control. A recent RCT (n=46) of participants with prediabetes and overweight or obesity showed that an ILED every other day for 12 months produced greater reductions (*P*<.05) in fasting insulin −52% (SE 9%) and insulin resistance -53% (SE 9%) compared with isocaloric daily moderate calorie restriction (−14%, SE 9%; −17%, SE 11%) despite similar decreases in body weight [26].

An ILED with 2 low-energy days per week will lead to a slower initial weight loss compared with a CLED. An unanswered research question is whether an ILED may lead to improved weight loss maintenance compared with daily dietary approaches in patients with T2D.

The relative benefits of ILED versus isocaloric CLED regarding glycemic control, diabetes remission, and weight loss maintenance in people with T2D are unknown.

### Remote Follow-up

A potential strategy for increasing adherence efficacy and reach of low-energy diet (LED) programs may be to include high-frequency remote follow-up, which has been shown to be superior to low frequency face-to-face care in weight management interventions [27]. Remote care reduces participants’ burden of attending face-to-face appointments and may be cost-effective compared with face-to-face care [28] while improving access to care. There is growing evidence to support the use of telehealth (including telephone and mobile phone–based apps) to monitor and provide feedback to patients with T2D and promote self-management of their condition [29-31].

The Manchester Intermittent versus Daily Diet Diabetes App Study (MIDDAS) incorporated high-frequency remote follow-up via the Oviva smartphone app and by telephone [32]. The app was used to facilitate self-monitoring of diet, weight, and blood glucose, and communication with HCPs, with the option of remote peer group support. Group participation in mobile apps has been shown to predict weight loss success [33]. Remote communities can be encouraging, motivating, and informative while remaining convenient and anonymous [34].

### Goals of This Study

The primary aim of MIDDAS is to assess the feasibility and potential efficacy of remotely supported ILED and isocaloric CLED programs in patients with overweight or obesity and T2D. The feasibility of an RCT comparing the 2 approaches was also assessed. MIDDAS did not have a control group for comparison because CLED programs have already been shown to be superior to standard or best practice.[13] The initial estimates of acceptability (uptake and retention) and potential efficacy (change in weight and glycated hemoglobin [HbA_1c_]) of the programs will determine whether progression to a full RCT is indicated and will inform the feasibility of delivering ILED and CLED programs that incorporate remote follow-up.

